
### Team training before the intervention

The researchers will draft training materials based on the Dietary Guidelines for Chinese Residents and guidelines from the Chinese Society of Nutritional Oncology. Then, the contents will be determined after a complete discussion with experts in various fields. After the intervention protocol is designed and three weeks before the formal implementation, three face-to-face training sessions will be conducted in the department meeting room; one training session will be provided per week, lasting approximately 2–3 h. During the first session, the oncologists and nurses will study the training materials and then teach other MDT members basic knowledge of BC and chemotherapy, coping methods for adverse reactions after chemotherapy, the relationship between hormones and diet among female BC patients, and the average weight standard for BC patients. Next, the researcher will introduce the necessity and feasibility of this multidisciplinary early intervention to improve patients’ DMB. During the second training, the dietitian and TCM practitioner will teach the team members how to carry out the targeted DMB intervention during the admission and home-based chemotherapy periods, how to guide patients in choosing an appropriate dietary nutrition supplement, the scientific methods of weight management, etc. Then, the researcher will provide a specific explanation of the flow and contents of the intervention. During the last session, the psychologist will introduce the necessity of maintaining a healthy mental state for cancer patients undergoing chemotherapy; analyze the standard sources, types, and factors related to pressure in BC patients; demonstrate strategies to help patients achieve stress relief; clarify the key points; and train patients to improve their self-management efficacy, self-regulation, and social support. Then, the researcher will further explain the frequency, time, division of work, and considerations of the intervention.

The training will include lectures, interactive workshops, case discussions, clinical practice, and scenario simulations. After the training, 5 BC patients treated with chemotherapy will be invited to participate in case analysis and scenario simulation, and the accuracy of the evaluation results will be discussed with the healthcare staff of the oncology department.

### Implementation of the multidisciplinary early intervention

A total of 8 intervention sessions will be conducted once a week, each lasting approximately 1.5–2 h. The intervention will begin during the early or middle stage of the whole chemotherapy cycle and continue through admission and a home-based interval chemotherapy period. During the first chemotherapy admission, patients will receive face-to-face group or individual interventions. During the home-based interval chemotherapy period, online meetings, WeChat messaging, or telephone calls will be adopted. The core elements of the 8 intervention sessions are listed as follows:

Intervention session 1 (topic: adverse reaction management): After the participants receive chemotherapy during admission and 1 day before hospital discharge, the MDT members will introduce themselves and the describe intervention process face-to-face, and patients will become familiar with each other. This session will include group interventions, group discussions and lectures: (1) patients will share their experiences with chemotherapy and diet; the group will discuss their own disease and chemotherapy experiences and diet change trajectory; (2) a nurse will show a professional video from the China Central Television (CCTV) “Health Road” program about BC, chemotherapy and diet; (3) oncologists, nurses, and dietitians will introduce the trend of common adverse reactions and the corresponding dietary self-management tips during different chemotherapy periods, including early, middle, and late-term chemotherapy or chemotherapy during admission or the interval period; and (4) oncologists will clarify the boundaries between dietary self-management and medication management when adverse reactions occur.Intervention session 2 (topic: dietary information and habit regulation): A combination of online group and individual intervention sessions will be conducted during the first week of the home-based interval chemotherapy period after session 1, which will include the following: (1) oncologists and dietitians will hold an online group Tencent conference to introduce authoritative sources of dietary information for cancer patients, such as WeChat public accounts, short videos, guidelines, and distributed information in the form of electronic materials; (2) dietitians and TCM practitioners will focus on correct dietary habits and misunderstandings for individuals with different demographic characteristics during telephone calls or WeChat messaging, including discussing the relationship between dietary intake and hormone levels for hormone receptor-positive patients, providing nutrition and weight management clinics and food therapy for patients with higher family income or abnormal weight; and (3) dietitians will demonstrate methods of dietary intake self-assessment by online video presentations, using simple and intuitive representations such as “a handful, a fist, 1 g or 2 g of quantitative salt spoons”.Intervention session 3 (topic: self-care self-efficacy training): The online group session during the second week of interval chemotherapy after session 1 will include the following: (1) nurses will guide patients to disclose their concerns about participating in their diet self-management; (2) the psychologist will lead “evidence check” and “advocate” sessions: patients will be asked to write evidence for and against their participation in dietary self-management on two post-it notes and then play the advocate, attacking the evidence against participation; and (3) nurses will provide diet option comparison cards to show patients the pros and cons of different dietary habits and encourage all patients to choose and share the reasons.Intervention session 4 (topic: treatment self-regulation training): Online group and individual sessions will be conducted during the third week of interval chemotherapy after session 1, which will include the following: (1) Through WeChat, the psychologist will send patients an assessment questionnaire linked to treatment self-regulation. According to the results, the patients will be divided into four groups: the autonomous motivation, introjected regulation, external regulation, and amotivation groups [31]. Then, the psychologist will explain definitions, content, and performance to the same online group Tencent conference; (2) the psychologist will explain the relationship between mood and diet and then use “identifying automatic thoughts” and “testing hypotheses” to determine the cognitive reasons for the lack of motivation among patients in the amotivation group in the process of participating in diet self-management and demonstrate stress relief techniques, such as deep breathing and listening to soothing music; and (3) nurses will invite patients in the autonomous motivation and introjected regulation groups to share their diet self-management experiences and the goals achieved.Intervention session 5 (topic: dietary supplement and TCM use): The next admission chemotherapy period after the session, which will include a face-to-face group lecture and discussion one day before hospital discharge, will include the following steps: (1) dietitians and TCM practitioners will use videos, charts, and paper materials to explain the concept, indications, and types of dietary nutritional supplements and replacement therapy (which can be divided into two categories: edible nutritional supplements as well as complementary and alternative therapies, such as moxibustion, massage, and aromatherapy); (2) through clinical practice and scenario simulations, using pictures or natural objects, oncologists and dietitians will guide patients in analyzing and choosing dietary supplements and replacement therapies according to their conditions; and (3) TCM practitioners will describe the content of food therapy that Chinese patients are interested in, popularize scientific knowledge and correct misunderstandings.Intervention session 6 (topic: social support seeking): Online group and individual sessions will be performed during the first week of home-based interval chemotherapy after session 5, which will include the following: (1) warm small things to share and express gratitude: nurses will encourage patients to write down the names of people who prepare their meals and living arrangements during chemotherapy through an online group Tencent conference and prepare a sentence, video or gift for them. (2) The psychologist will provide targeted dietary management tips related to emotion and psychology depending on the working status of patients via WeChat or telephone. For employed females, dietary advice will be provided to their families or colleagues before they return to work. Nonemployed individuals will be encouraged to share their thoughts and preferences regarding their diet with friends or neighbors who would like to help take care of them. (3) Nurses will encourage patients to share how others can help improve their diet during chemotherapy and how they seek help.Intervention session 7 (topic: weight management): Online group and individual sessions will be provided during the second week of the interval chemotherapy period after session 5, which includes (1) oncologists informing patients that being overweight is a risk factor and showing patients how to correctly measure their body weight via an online video, calculate their body mass index (BMI) and determine their BMI classification. (2) Dietitians will introduce the criteria and ranges of daily caloric intake for patients with different BMI classification via WeChat or telephone. For example, overweight and obese patients will be taught to read ingredient lists and recipes. Patients with a BMI below the normal range will be taught to choose foods rich in high-quality fat (such as omega 3 fatty acids and monounsaturated fatty acids) and protein [29, 30]. Repeated operations and repetitions will be used to test the effect. (3) Nurses will show patients and their caregivers how to exercise moderately and record daily calories using apps or memos.Intervention session 8 (topic: outcome expectation education): An online group session during the third week of interval chemotherapy after session 5 will include the following: (1) the psychologist will introduce the concept, content, necessity, classification and function of the outcome expectation related to dietary self-management to patients by an online group Tencent conference; (2) Nurses will encourage patients to write down their expectations for diet self-management on post-it notes and classify them into immediate or future goals; (3) The psychologist will use the “five-column chart” of alternative thinking to ask patients to share their views on the outcome expectations and determine the negative cognition of achieving the goal; (4) Through scenario and case studies, the psychologist will lead patients to analyze their own cognition on two outcome expectations of what points may be right or wrong, encourage them to create new goals and teach them how to stick to long-term dietary self-management monitoring; and (5) MDT members will summarize and share the gains and suggestions of this intervention with patients.

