### Sample size

G power software will be used to calculate the sample size of the study, and ANOVA and a priori power analysis were selected [27]. Because there is little relevant literature and most multidisciplinary health management interventions do not report detailed sample size calculation parameters, we adopted system default parameters, including an effect size of 0.25, a power of 0.95, and an α of 0.05. After calculation, the total sample size was 72, with 36 participants in each group. Considering a 20% loss-to-follow-up rate, we obtained a final sample of 44 participants per group.

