### Statistical analysis

We will use IBM SPSS Statistics 21.0 software to analyze the statistical data. Descriptive statistics, such as the number of patients with different ages, education levels, cancer stages and types of chemotherapy, as well as the percentage of patients in different groups relative to the total number of patients, will be calculated for different groups of demographic and clinical information. The mean and standard deviation will be used to compare the DMBQ total and dimensions scores, the SUPPH and FACT-B scores, and BMI. To compare the baseline balance between the two groups, two independent sample *t* tests, chi-square tests or Mann‒Whitney U tests, will be used, depending on whether the data distribution satisfies homogeneity of variance. The Shapiro‒Wilk test will be used to verify whether the scores of the two groups at different time points follow a normal distribution. If the data are balanced, repeated ANOVA will be adopted. Otherwise, we will use a generalized estimating equation (GEE) to analyze the intervention’s time, group, and interaction effects [36]. For all the above tests, *P* < 0.05 will indicate a statistically significant difference, the α level will be 0.05, and the tests will be two-sided. We will use intention-to-treat (ITT) analysis to minimize bias for sensitivity analysis [37]. The results of the last measurement of the patients who drop out of the study will be taken as the effect, which assumes that they complete the intervention, and the analysis will be reconducted with the GEE. Furthermore, missing data will be imputed with the mean values of the characteristics or with the help of multiple imputation methods if they are random and unrelated to the research elements.

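### The intervention is delivered largely in patient groups, but the sample size and the named analyses make no allowance for correlation among patients who attend together

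*Protocol article*

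**What the plan says.** **Delivery** (Implementation of the multidisciplinary early intervention). Sessions 1, 3, 5 and 8 are described as group sessions, and sessions 2, 4, 6 and 7 as a mix of group and individual work. Of session 1 the article says "This session will include group interventions, group discussions and lectures", and it intends that "patients will become familiar with each other". In later sessions patients voice their concerns, compare diet choices and present their goals to one another. Individual delivery is also possible: at the first admission "patients will receive face-to-face group or individual interventions".

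**Sample size.** The article reports that "ANOVA and a priori power analysis were selected" and, for the inputs, that "we adopted system default parameters", "including an effect size of 0.25, a power of 0.95, and an α of 0.05". This gives 72 patients, raised to 88 for 20% loss. No group size, ICC or design effect appears.

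**Statistical analysis.** "If the data are balanced, repeated ANOVA will be adopted"; otherwise a GEE will examine time, group and interaction effects, where group means trial arm. For significance, "the α level will be 0.05, and the tests will be two-sided". No level for session group is named.

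**Elsewhere.** The fidelity checklist notes a head count per group but is not said to record who was in it (Intervention fidelity). Usual care includes group lectures, with online conferences as needed (Control group: usual care).

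**The concern.** Patients are randomised one by one, but those in the intervention arm are then treated together. Discussion, peer influence and shared providers can make the outcomes of patients in one session group more alike than those of patients in different groups. The primary questionnaire covers coping with adverse reactions, finding dietary information, regulating habits and using supplements, which are the topics the groups discuss. The structure is partially nested: intervention patients sit within session groups, while controls have no comparable series of sessions.

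Repeated-measures ANOVA handles correlation between the six assessments of one patient. It does not handle correlation between patients. A GEE clustered on the patient has the same limit. With positive within-group correlation, the mean of the intervention arm is less precise than 44 independent patients would make it. The interval for the primary effect is then too narrow, its P value too small, and the planned power too optimistic.

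**Working it through.** **1. The plan's own figure.** With f = 0.25, alpha 0.05, power 0.95 and two arms, noncentral-F calculations give a total of 210 for a one-way ANOVA. For repeated measures with correlation 0.5 and six assessments they give 124 for the between-arm test and 28 for the interaction. No two-arm variant with correlation 0.5 and two to six assessments gives 72. The figure 72 does appear under settings the article does not state:
- between-arm test, 3 assessments, correlation 0;
- between-arm test, 6 assessments, correlation 0.2;
- interaction test, 4 assessments, correlation 0.

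The 72 therefore cannot be reproduced uniquely, but each of these variants treats patients as independent. The loss step is acceptable: 36 × 1.2 = 43.2, rounded up to 44 per arm (36 / 0.8 would give 45).

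**2. Inputs for the clustering check.** From the article: 44 patients per arm, two-sided alpha 0.05, power 0.95. Assumed: ICC ρ from 0.01 to 0.10, and group size m. One guide to m comes from the Randomization section, which plans 88 patients in 3 months. Even intake means 44 / 13 weeks ≈ 3.4 intervention patients a week. Larger groups need several weeks to be pooled, which the article neither states nor excludes, so m = 8 and m = 11 are shown as well.

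**3. Formulas**, for one difference in means with clustering in the intervention arm only:
- design effect in that arm: D = 1 + (m − 1)ρ
- variance multiplier of the arm difference: V = (1 + D) / 2
- correct SE divided by naive SE: √V
- type I error of the naive test: 2[1 − Φ(1.96 / √V)]
- power of a test using the correct SE, planned at 95%: Φ((1.96 + 1.645) / √V − 1.96)
- intervention patients' worth: 44 / D
- evaluable total needed: 72 × V, rounded up to whole patients per arm

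**4. Worked case**, m = 8 and ρ = 0.05. D = 1 + 7 × 0.05 = 1.35. V = 2.35 / 2 = 1.175 and √V = 1.084. Type I error = 2[1 − Φ(1.808)] = 7.1%. Power = Φ(3.605 / 1.084 − 1.96) = Φ(1.366) = 91.4%. Worth of the arm = 44 / 1.35 = 32.6. Evaluable total = 72 × 1.175 = 84.6, so 86.

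**5. Range**

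| m | ρ | D | √V | Type I error | Power | Worth of 44 | Evaluable total |
|---|---|---|---|---|---|---|---|
| 3.4 | 0.01 | 1.02 | 1.006 | 5.1% | 94.8% | 43.0 | 74 |
| 3.4 | 0.05 | 1.12 | 1.030 | 5.7% | 93.8% | 39.3 | 78 |
| 3.4 | 0.10 | 1.24 | 1.058 | 6.4% | 92.6% | 35.5 | 82 |
| 8 | 0.01 | 1.07 | 1.017 | 5.4% | 94.3% | 41.1 | 76 |
| 8 | 0.05 | 1.35 | 1.084 | 7.1% | 91.4% | 32.6 | 86 |
| 8 | 0.10 | 1.70 | 1.162 | 9.2% | 87.3% | 25.9 | 98 |
| 11 | 0.01 | 1.10 | 1.025 | 5.6% | 94.0% | 40.0 | 76 |
| 11 | 0.05 | 1.50 | 1.118 | 8.0% | 89.7% | 29.3 | 90 |
| 11 | 0.10 | 2.00 | 1.225 | 11% | 83.7% | 22.0 | 108 |

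At ρ = 0 nothing changes. The number of groups would be about 13 (m = 3.4), 5 or 6 (m = 8) or 4 (m = 11). These are normal approximations and leave out the further uncertainty that comes with few groups.

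**The case against.** **The effect is assumed, not shown.** The article gives no ICC and no group size. Session 1 is held the day before discharge, which limits a face-to-face group to patients leaving at about the same time. With even intake and small groups, the loss is modest. This stands, and the statement must be conditional.

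**Inflation of type I error needs a particular null.** Patients are randomised individually. If the sessions change nobody's outcome, sitting together creates no correlation, and the patient-level test keeps its level. Inflation arises when the average effect is zero but session groups shift outcomes in different directions. This stands. It does not rescue the interval or the power: if the sessions work to a degree that varies by group, the naive interval is too narrow whatever the average effect. The formulas also address one difference in means, whereas the plan tests arm, time and interaction over six assessments, where the relevant ICC may differ.

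**The contrast between arms is not clean.** Controls attend group lectures and may join online conferences, so some clustering is possible there too. That would add variance rather than remove the problem, and no fixed series of interactive sessions is described for controls.

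**Groups may shift.** Individual delivery is allowed at the first admission, session 4 sorts patients by type of motivation, and session 5 depends on the next admission. Each may dilute the correlation. This is a reason to record actual attendance.

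**The cluster level of the GEE is not stated.** A reader might infer that it is the patient, but the article does not say, and that detail may lie in a document not shown. The point is therefore firmer for the repeated-measures ANOVA and for the sample size, whose inputs the article does state.

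**Conclusion.** The point holds in conditional form. The article describes group delivery throughout the intervention, while its sizing and its named analyses contain nothing for correlation within session groups. Any positive correlation makes the standard error of the arm difference too small and puts power below 95%.

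The size is uncertain. For ICC 0.01 to 0.10, type I error is about 5.1% to 6.4% with groups of about 3.4 and reaches about 11% only at the far corner, ICC 0.10 with groups of 11. The middle case, ICC 0.05 with groups of 8, gives 7.1% and power of about 91%, but the article offers no basis for groups of 8 in particular.

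A reader might go further and infer that the standard errors are certainly wrong, that the 44 intervention patients are known to be worth about 33, or that controls have no group contact at all. The documents do not support these readings: no ICC or group size is given, and usual care includes group lectures. The point is worth acting on because the direction is clear, the remedy is cheap, and membership may not be recoverable if it is not recorded during the trial.

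**What to change.** 1. **Record membership.** For each intervention patient, record the session group actually attended, with the session 1 cohort as the main identifier and later changes noted. A patient treated individually forms a group of one. Weekly attendance is already tracked under Adherence to the intervention, so this adds one data field. Delivery stays as it is.
2. **Allow for it in the primary analysis.** Either fit a partially nested mixed model, with a random session-group effect in the intervention arm, a patient random effect for the repeated assessments and small-sample degrees of freedom (such as Satterthwaite), or use a GEE clustered on session group with a small-sample correction. This replaces the named repeated-measures ANOVA for the primary outcome, so it should be settled before the data are analysed.
3. **Report** the estimated ICC with its interval.
4. **Qualify the sample size statement.** Say that the 95% power holds only without within-group correlation, and show power over a stated range of ICC and group size.

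The cost is one data field, a change of model and slightly wider intervals. With roughly 4 to 13 groups the ICC will be imprecise, so it should be read with its interval. The model also leaves out any clustering from the controls' group lectures, which should be stated as a limitation.

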### Study design

A prospective 8-week, two-arm, single-center, single-blinded parallel-group RCT with a pretest and follow-up will be conducted by an MDT. Female patients who are diagnosed with BC and waiting to start chemotherapy or who are in the early or middle stage of chemotherapy will be randomized to receive either usual dietary care or the multidisciplinary early dietary management intervention. The participants in the intervention group will receive the multidisciplinary early intervention measures constructed based on the ITHBC. In contrast, the control group will receive only the usual cancer dietary care education at admission and education manuals based on the Dietary Guidelines for Chinese Residents, the World or American Guidelines, etc. The intervention consists of the following eight themes, with sessions provide once per week: adverse reaction coping, dietary information and habit regulation, self-care self-efficacy training, treatment self-regulation training, dietary supplement and TCM use, social support seeking, weight management, and outcome expectation education. Detailed information is provided in Fig. 1. Eight intervention sessions will be provided throughout admission for chemotherapy and a home-based interval chemotherapy period. This intervention will be initiated during the early and middle stages of chemotherapy. Standard chemotherapy cycles include 4, 6, and 8 cycles. For example, for patients receiving 4 chemotherapy cycles, the first intervention session will be provided during the first or second admission for chemotherapy. For patients receiving 6 cycles, the first intervention session will be provided during the first, second, third, or fourth admission. For patients receiving 8 cycles, the first intervention session will be provided during the first, second, third, fourth, fifth or sixth admission. The duration of intervention sessions during different chemotherapy cycles is shown in Fig. 2. In addition to the baseline measurements, follow-up measurements were taken immediately after the end of the intervention (T_1_) and at 1 (T_2_), 3 (T_3_), 6 (T_4_) and 12 months (T_5_) after the intervention. T_1_ was measured immediately after the end of the eighth intervention session. T_2_, T_3_, T_4_ and T_5_ will be measured 30, 90, 180 and 360 days after the T_1_ measurement date, respectively. The intervention process is shown in Fig. 3. The same time points for follow-up in the intervention group will be also used for the control group.

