### Control group: usual care

The patients assigned to the control group will receive standard admission health education from the department. The main contents include the following: After the BC patients are admitted to the hospital, the doctor will ask about the patient’s condition and provide basic BC disease information. Nurses will distribute health education manuals, such as adverse reactions and coping methods related to chemotherapy. In addition, oncologists and nurses will provide clinical group lectures to explain the relationship between chemotherapy and diet, dietary information and strategies (mostly from the Dietary Guidelines for Chinese Residents, the World or American Guide, etc.), the necessity of weight management, etc. Health professionals will use face-to-face communication, question answering, demonstrations, and other methods during admission for chemotherapy to solve dietary problems. Patients who need food therapy will be evaluated by doctors and provided with relevant knowledge, precautions, indications and contraindications. During the home-based chemotherapy interval, telephone calls, WeChat messaging, online conferences, emails, and other forms of assistance will be provided to BC patients as needed. As is usual practice, no specific or individual recommendations will be provided.

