#### BMI

To minimize bias, we will provide each patient with an electronic weighing scale of the same make, model, and batch. The patients will be told to perform measurements in the morning after defecation and urination, wearing only underwear. Considering the limitations of the patients’ ages and educational levels as well as to improve operability, direct input of data by the patients will be avoided. Patients will be asked to weigh themselves at 7–8 am, and the data will be uploaded to their bound app and sent to the researchers via a screenshot. Screenshots of each measurement for each patient will then be recorded, checked by two researchers, entered into statistical software, and automatically saved in the cloud. The screenshot will show the specific date, time, and weight value. Height will be recorded after being measured using the hospital’s anthropometer at the patient’s initial admission. BMI will be calculated directly by using the formula in the statistical software.

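### All patients get the same weighing instruction, but only the intervention arm is also shown a weighing video, after T0 and shortly before T1 (minor; BMI only)

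*Protocol article*

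**What the plan says.** **Common procedure.** The BMI section of the protocol article sets one procedure and does not limit it to an arm. On equipment: "To minimize bias, we will provide each patient with an electronic weighing scale of the same make, model, and batch". On conditions: "The patients will be told to perform measurements in the morning after defecation and urination, wearing only underwear". On timing and capture: "Patients will be asked to weigh themselves at 7–8 am, and the data will be uploaded to their bound app". Two researchers check each screenshot, and of its content the article says: "The screenshot will show the specific date, time, and weight value". Height is measured in hospital. According to Data collection, BMI is part of every assessment.

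**Extra element in one arm.** Under Implementation of the multidisciplinary early intervention, session 7 (weight management) includes "showing patients how to correctly measure their body weight via an online video". On its timing: "Online group and individual sessions will be provided during the second week of the interval chemotherapy period after session 5". Session 8 follows in the third week of that interval. Study design says that T1 "was measured immediately after the end of the eighth intervention session", and T2 to T5 are counted from T1.

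**Control arm.** On weight, Control group: usual care lists only "the necessity of weight management, etc". It describes no weighing video or demonstration. Controls are assessed at the same time points.

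**Status of BMI.** The Abstract names it as a secondary outcome. The body places it under Other outcomes.

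**The concern.** Instruction in how to measure an outcome should be the same in both arms and complete before baseline. Here part of it sits inside the tested intervention. An intervention patient weighs at T0 with the common instruction alone and at T1 to T5 with the instruction plus the video. A control patient has the instruction alone throughout.

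If the video changes how patients weigh themselves, recorded BMI can shift in one arm after baseline with no change in body weight. The planned repeated-measures ANOVA or GEE tests the group-by-time interaction and would read such a shift as an effect of the intervention. No later analysis could remove it, because nothing records whether the clothing and voiding conditions were met.

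**Working it through.** **1. Sequence by arm.**

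| | Before T0 | Between T0 and T1 | T1 to T5 |
|---|---|---|---|
| Intervention | same scale, told the conditions | weighing video (session 7) | instruction plus video |
| Control | same scale, told the conditions | no video described | instruction only |

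Sessions 7 and 8 fall in the second and third week after session 5, and T1 follows session 8 directly. So the video comes about one week before T1. T0 precedes it and every later assessment follows it.

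**2. What the safeguards cover.** The identical scale covers the device. App capture and the double check cover transcription. The time stamp covers the 7 to 8 am window. None of them covers clothing or voiding.

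**3. Size, for illustration.** The article gives no height, technique error or SD of BMI change, so there is no figure of its own to reproduce. Inputs:

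- From the article: 44 randomised and 36 analysed per arm (Sample size); two-sided α of 0.05 (Statistical analysis).
- Assumed: height 1.58 m; a weighing outside the stated conditions reads 0.5 to 1.5 kg too high; after T0 such weighings are 20 to 40 percentage points more frequent in controls; SD of BMI change 1.0 to 1.5 kg/m².

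Shift per affected weighing = kg / height²:

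- 0.5 / 1.58² = 0.5 / 2.496 = 0.20 kg/m²
- 1.0 / 2.496 = 0.40 kg/m²
- 1.5 / 2.496 = 0.60 kg/m²

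False arm difference = excess share × shift:

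- low: 0.2 × 0.20 = 0.04
- middle: 0.3 × 0.40 = 0.12
- high: 0.4 × 0.60 = 0.24 kg/m²

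Standard error = SD × √(2/n). With δ = difference / SE, the two-sided rejection rate when the intervention has no effect is Φ(−1.96 − δ) + Φ(−1.96 + δ).

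| n per arm | SD | SE | δ at 0.04 / 0.12 / 0.24 | Rejection rate |
|---|---|---|---|---|
| 44 | 1.0 | 0.213 | 0.19 / 0.56 / 1.13 | 5.4% / 8.7% / 20.3% |
| 36 | 1.0 | 0.236 | 0.17 / 0.51 / 1.02 | 5.3% / 8.0% / 17.5% |
| 44 | 1.5 | 0.320 | 0.13 / 0.38 / 0.75 | 5.2% / 6.6% / 11.7% |
| 36 | 1.5 | 0.354 | 0.11 / 0.34 / 0.68 | 5.1% / 6.3% / 10.4% |

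**4. Boundary case.** If both arms keep to the common conditions from T0 on, the excess share is 0, the false difference is 0 and the rate stays at 5%. If BMI were compared without using the baseline, with an assumed raw SD of 3.5, the highest assumed bias would give only about 6%.

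**The case against.** The best reply is that the article already standardises weighing for everyone: same scale, time window, voiding and clothing rules, and automatic capture, with the stated aim of limiting bias. The video comes on top of that, its content is not shown, and it may only repeat the common instruction. This stands. A reader might infer from session 7 that controls, and all patients at T0, weigh themselves untrained, or that the conditions are mentioned only once. The BMI section does not support either reading. It instructs patients in both arms and says nothing on how often they are reminded.

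The mechanism also needs a particular pattern: control patients, and intervention patients before session 7, depart from the instruction, and intervention patients then improve. The article gives no sign of this. Nor does it set a desired direction for BMI, since session 7 advises overweight patients and those below the normal range differently. A small downward shift would therefore not translate directly into a claim of benefit.

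What the reply does not remove is the asymmetry itself. If the video adds nothing, it is not needed in session 7. If it improves technique, it does so in one arm only. The safeguards cannot show which of these happened.

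**Conclusion.** The point holds as a minor one. One arm receives an additional lesson in measuring an outcome, after baseline and before every later measurement. This touches BMI only. The primary DMBQ, the SUPPH and the FACT-B are unaffected.

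The documents do not fix the size. It is near zero if the common instruction is followed in both arms from T0. Under the assumed partial non-adherence, the false difference is 0.04 to 0.24 kg/m² and the false-positive rate about 5% to 20%. The upper end needs the largest assumed error, the largest assumed gap between arms, the smaller SD and no dropout, all together. The middle case gives about 6% to 9%. The direction, towards lower BMI in the intervention arm, rests on the assumption that faulty weighings read too high.

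A reader might go further and conclude that the BMI comparison is invalid or that its error rate is known to be inflated. The documents do not support that: every input to the bias is assumed, and the shared instruction may be enough.

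**What to change.** Show the same weighing video to every patient in both arms when the scale is handed out, before the T0 weighing, and say so in the BMI section. Take that element out of session 7, which keeps BMI calculation, classification and advice.

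The cost is a few minutes at baseline for 88 patients, using a video that is already planned. One small element of session 7 is then no longer specific to the intervention. Sample size, outcomes and analysis stay as they are.
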